**Figure 1 BMJOPEN2016012684F1:**
[figure not shown]
Participant flow through the HOME BP study. GPs, general practitioners; HOME BP, Home and Online Management and Evaluation of Blood Pressure.

#### Sample size consideration

A sample size of 244 patients per group is required in order to have 90% power to detect a difference in SBP of 5 mm Hg (SD 17 mm Hg) between intervention and control groups, based on the findings from the TASMINH-2 study.^20^ Allowing for a 15% participant drop out, we will seek to recruit 287 participants per condition, resulting in a total sample size of 574 participants.

#### Recruitment

On the basis of our pilot work, and previous experience from hypertension self-management interventions,^21^ we estimate an approximate recruitment rate of 4% from the practice invite mail-out. Assuming an average practice list size of 5000, with a prevalence of hypertension of 13%, it is estimated that ∼75% of the hypertension register will be excluded based on last BP reading and other practice exclusions. We estimate that ∼15% of patients invited will attend a baseline screening appointment, with ∼50% ineligible due to low BP readings during the screening appointment. We also estimate that a further 50% may decide not to participate due to the online format of the intervention. Around 95 practices are therefore likely to be required in order to recruit the target number of participants (n=574).

### HOME BP intervention

The HOME BP intervention consists of HOME BP online (for patients and healthcare professionals), BP self-monitoring, medication titration procedures and optional behavioural support. Each of these components is described below, guided by the TIDieR checklist where possible.^37^ The intervention was developed using a theory-based, evidence-based and person-based approach,^38^ which is fully described elsewhere (article in submission).

#### HOME BP online: patient behavioural components

HOME BP online will use behavioural techniques to build patient motivation for BP self-monitoring, medication adherence and medication titration ([name], [name], [name], *et al*. Intervention planning for a digital intervention for self-management of hypertension: a theory-, evidence- and person-based approach. *Implement Sci*. In submission). This will include presenting the health-related benefits of self-monitoring and reducing BP through medication titration procedures. Positive patient outcome expectancies will be encouraged by outlining ways that using the HOME BP intervention may reduce the chances of experiencing negative health consequences associated with hypertension. Common patient concerns regarding medication side effects are also addressed.

Patients will be instructed how to correctly undertake self-monitoring to promote patient self-efficacy. An Omron M3 monitor will be given to intervention group participants, and training provided through HOME BP online using a demonstration video. Participants will be asked to rehearse self-monitoring for a minimum of 7 days and enter their practice readings into HOME BP online before they are able to undertake study procedures. Participants will be able to print off tables to record each day's readings off-line and then enter all seven readings at one time (see figure 2 for screenshots of the intervention pages). Patients will also be provided with examples of successful hypertension management using HOME BP procedures to further increase self-efficacy for BP management.

**Figure 2 BMJOPEN2016012684F2:**
[figure not shown]
Screenshots of HOME BP pages. HOME BP, Home and Online Management and Evaluation of Blood Pressure.

Nine weeks after participants have been allocated to HOME BP, a behaviour change choice tool outlining the specific benefits of user-selected lifestyle modifications targeting healthy eating, physical activity, losing weight and salt and alcohol reduction will be available within HOME BP online. Users will be have the option of reading guidance about the benefits and commitments of each lifestyle change, so that they can choose the one (or more) which would be best for them. Patients will be reassured that additional behavioural support will be provided by their practice HOME BP support provider (usually a nurse or healthcare assistant) for self-monitoring or lifestyle modifications, if required. The rationale for providing these options 9 weeks after the intervention began was to avoid making multiple behaviour changes^39^ until participants had an opportunity to form habits around the key target behaviours of self-monitoring and medication adherence.^40^

#### HOME BP online: healthcare practitioner behavioural components

HOME BP online will build healthcare practitioner motivation, knowledge, skills, positive outcome expectations and self-efficacy for study procedures, particularly medication titration. Healthcare practitioner self-efficacy will be promoted by addressing concerns regarding patient titration acceptance; the reliability of home blood-pressure readings and study procedures as an effective tool for overcoming clinical inertia for patients and practitioners will be outlined. Evidence demonstrating the health-related benefits of the medication titration procedure will be presented, in addition to evidence indicating that the medication escalation procedures do not result in increased patient side effects.^14^
^20^
^21^ Users will be provided with information about the study procedures specific to their role (ie, prescriber or support provider) and information relating to study safety procedures.

Patients and healthcare practitioners will be able to re-access their specific behavioural intervention components from HOME BP online at any time throughout the study.

#### Self-monitoring procedures

Patients will be advised to take two morning BP readings for 7 days each month and in each case to use the second reading (as per the TASMINH2 and TASMIN-SR studies).^20^
^21^ Automated email prompts will be sent to participants as reminders to begin BP self-monitoring. Patients will need to have seven readings to enter into HOME BP online, but will be able to flexibly complete their readings over a 2-week period if required. Following the completion of each set of seven readings, patients will have access to the behavioural intervention components described above, but will not enter further BP readings for further 4 weeks.

#### BP targets

BP targets will be set in line with the National Institute for Health and Care Excellence (NICE) hypertension guidelines,^41^ with adjustment by 5/5 mm Hg for home readings.^42^ People under 80 without diabetes will have BP targets of <135/85 mm Hg, while patients aged 80 and over without diabetes will have a target BP of <145/85 mm Hg. Target BP for all patients with diabetes will be <135/75 mm Hg (those with proteinuria and therefore lower targets are excluded). After the seven readings are entered in to HOME BP online, the mean BP will be calculated and feedback provided to the patient and the healthcare practitioners according to a traffic light system (developed from that used in previous medication titration procedures).^20^
^21^ These readings will be used to inform the medication titration procedure.

#### Medication titration procedures

All HOME BP prescribers will receive a copy of the NICE hypertension guidelines^41^ and will complete an individualised patient medication review at baseline for intervention group participants, where three potential medication changes will be selected and agreed with the patient. If a patient's mean BP readings are above target for two consecutive months, the medication titration procedure will be initiated by HOME BP online. Patients and practice staff will be informed by email that a medication change is recommended. The prescriber will be asked to implement the preplanned medication change and confirm this with the patient (or explain the reasons for non-implementation, if applicable). If patients decide not to initiate a medication change, the prescriber will receive information provided by the patient outlining the reasons for non-titration. When a recommended medication change is not initiated, an above target reading at the subsequent BP entry will again prompt a medication change recommendation from HOME BP online.

If patients take two BP readings that are too high (>180/110 mm Hg) or low (SBP <100 mm Hg), they will be asked to repeat the measurement after 5 min. If readings are still too high or too low, the HOME BP healthcare practitioners will be alerted by email and patients will be advised to make an appointment with the prescriber in the usual way within 3 days. Decisions about patients' medication will remain at the prescriber's discretion at all times. If a mean target BP (ie, below target but SBP above 100 mm Hg) is entered into HOME BP online for three consecutive months, patients will be advised to reduce BP monitoring to once every 8 weeks as their BP is currently well controlled. This will revert to monthly should subsequent mean BP rise above target.

#### HOME BP behavioural support

Optional additional behavioural support for self-monitoring and lifestyle modifications will be available to all patients via the practice support providers, who will be trained in applying the CARE (Congratulate, Ask, Reassure, Encourage) approach (paper outlining this approach in HOME BP forthcoming). A face-to-face appointment is offered to all participants at 4 weeks following randomisation and 1 week after any lifestyle modifications are introduced, with an option for remote telephone or email support if preferred. A maximum of six face-to-face support sessions will be available if patients experience difficulties associated with self-monitoring or lifestyle change, and patients will have the option to email their support provider through HOME BP online at any point. Template-guided motivating and reassuring support messages will be sent by email from the support provider to all patients every 4 weeks to encourage and reinforce patient adherence to monitoring, medication regimes and lifestyle changes (where applicable).

#### Monitoring adherence

Automated email reminders will be sent to patients and healthcare practitioners at key milestones to promote adherence to study procedures. Adherence to titration procedures will also be monitored by the healthcare practitioners and study team to ensure changes have been enacted (or to understand why not). At the end of the study, each HOME BP supporter will return a copy of their support log. An audit of a selection of BP monitors will be conducted.

### Usual care

Patients allocated to usual care will have access to the information provided in the Blood Pressure UK patient leaflet for hypertension through HOME BP online. They will receive routine hypertension care, with appointments and medication changes made at the GP's discretion.

### Outcomes

The primary outcome of the trial will be difference in office SBP (mm Hg, mean of second/third readings) at 12-month follow-up between the intervention and control groups adjusting for baseline BP, practice, BP target levels and gender. These will be entered and stored on an independent, secure server.

Secondary outcomes (also adjusted for baseline and covariates where appropriate) will comprise:
Difference in office SBP between intervention and control groups at 6-month follow-up.Difference in office DBP between intervention and control groups at 6-month and 12-month follow-up.Difference in office SBP and DBP at 6 and 12 months using the mean of the second to sixth BP readings.Difference in health-related quality of life measured using EQ-5D-5L.^43^Difference in patient enablement measured using the patient enablement instrument.^44^Economic modelling (including cost of equipment and drugs, patient and healthcare professional time and support provision).

Process evaluation measures will include:
Medication beliefs measured using the Beliefs about Medicines Questionnaire (BMQ)^45^ and medication adherence using the Medication Adherence Report Scale (MARS).^46^Patient perceived side effects measured using the symptom subscale of the Illness Perception questionnaire (IPQ-R) hypertension.^47^Patient self-efficacy.^48^Medication use (number and defined daily doses).^49^Patient weight measured within clinic and self-reported lifestyle behaviours.Prescriber and support provider self-efficacy and outcome expectations.Prescriber and support provider confidence in the acceptability of the intervention.

Intervention group only:
DI website usage and engagement, including lifestyle choice, usage and progress.Patient BP monitoring adherence measured by the HOME BP online system.Adherence to recommended medication changes.Usage of optional support provision.Prescriber initiation of titration procedures.

### Adverse events

HOME BP healthcare practitioners will inform investigators of all patient adverse events occurring throughout the trial. The assessment of whether or not an serious adverse event (SAE) is an expected consequence of receiving the intervention will be provided by the chief investigator (or clinical reviewer delegate), it will not be provided by the investigator responsible for the care of the participant.

### Study end points

Participants in the intervention and control groups will be invited to appointments with an independent research nurse for assessment of primary and secondary end points at 6 months and 12 months following entry into the study. These appointments will be conducted in the same way for both groups. Any other contacts with the GP practice (outside of the study) will be recorded in the medical notes and reported for the economic analysis at the end of the trial (based on blind review of patient medical notes). Only members of the study research team involved in the data collection, and data analysis will have access to the final trial data set.

### Measures

See table 1 for full details of study measures.

**Table 1 BMJOPEN2016012684TB1:** Measures and schedule of observations within the HOME BP trial

	Time point				
Measure	Baseline/screening	Visit 1	Visit 2	Intervention group only	Usual care group only
Month	0	6	12	(0–12)	12
Patient sociodemographic measures	X				
Frequency of previous self-monitoring	X				X
Clinical measures					
Systolic BP (SBP)	X	X	X		
Diastolic BP (DBP)	X	X	X		
Weight (kg)	X		X		
Height (cm)	X				
Diabetes status	X				
Hypoglycaemic episodes in last 6 months	X	X	X		
Medication changes (prescriptions issued)			X (NR)		
Consultations			X (NR)		
Patient self-report measures					
Patient enablement instrument	X		X		
Patient self-efficacy	X	X	X		
Beliefs about medication (BMQ)	X	X	X		
Medication adherence (MARS)	X		X		
Patient perceived side effects (IPQ-R hypertension: symptoms subscale)	X		X		
Changes to lifestyle behaviours			X		
Patient objectively recorded measures					
Website usage				X*	
Usage of hypertension pages				X*	
Monitoring of blood pressure					
Self-reported SBP				X*	
Self-reported DBP				X*	
Medication titration recommended				X*	
Titration uptake				X*	
Reasons for non-titration				X*	
Usage of lifestyle pages				X*	
Choice of lifestyle changes				X*	
Reported progress on lifestyle change (eg, weight change)				X*	
HCP objectively recorded measures					
Usage of training pages (prescriber guide)				X	
Emails sent to the patient				X	
Titration procedure compliance				X	
Support provision				X	
HCP self-report measures					
Self-efficacy and outcome expectations	X†				
Confidence in the acceptability of the intervention (for patients)	X†				
Economic measures					
Patient quality of life (EQ-5D)	X	X	X		
Costs of equipment and drugs			X(NR)		
Health professional time			X(NR)		
Patient time			X(NR)		
Qualitative process analysis					
Patient experience and views of the HOME BP				X	X
HCP experience and views of the HOME BP				X	X

*HOME BP intervention arm only—measured throughout the study via HOME BP online.

†Measured directly before and after the HOME BP online training completion.

HOME BP, Home and Online Management and Evaluation of Blood Pressure; NR, notes review.

### Statistical analysis

The principal analysis will use raw and adjusted data and will be performed at the end of the trial after all data have been collected. The primary analysis will use general linear modelling to compare intervention and usual care SBP at follow-up adjusting for baseline BP, practice (as a random effect), BP target levels and gender. Analyses will be on an intention to treat basis with imputation. Secondary analyses will be reported for complete cases. No interim analyses will be performed. A sensitivity analysis will examine the potential effect of missing data using multiple imputation. Planned subgroup analyses will be of BP target groups, older versus younger (65 as threshold), men versus women and better controlled at baseline versus worse controlled at baseline (median SBP). Secondary analyses will use similar techniques to assess differences between groups in SBP at 6 months, DBP at 6 months and 12 months, medication use and quality of life. Additional analyses will examine patient and healthcare professional adherence to advice and study processes, website usage and support provision. Process analyses will be reported elsewhere, but will assess the impact of patient enablement and self-efficacy, symptom perceptions and medication beliefs on outcomes. These analyses will also examine the relationship between support uptake, engagement with healthy behaviour change and outcomes.

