#### Randomisation

Participants will be randomised in a 1:1 ratio to receive either usual care or the HOME BP intervention with optional nurse support using the HOME BP online system. Minimisation will be used taking into account participants' baseline SBP, age, diabetes status and practice. Patients are randomised to the optimal group 80% of the time. Any random numbers the minimisation routine might need will be computer generated, therefore bypassing study team involvement.

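### Age is a minimisation factor but enters the primary model only through the age-80 cut in BP target level, so the model-based standard error will tend to be slightly too wide

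*Protocol article*

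**What the plan says.** The Randomisation section sets the allocation method: "Minimisation will be used taking into account participants' baseline SBP, age, diabetes status and practice". The ratio is 1:1, and the favoured arm is assigned with probability 0.8 ("Patients are randomised to the optimal group 80% of the time").

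The covariates of the primary model are listed twice, with the same content. Outcomes has "adjusting for baseline BP, practice, BP target levels and gender". Statistical analysis has "adjusting for baseline BP, practice (as a random effect), BP target levels and gender". Neither list names age.

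The BP targets section defines the target levels. Patients without diabetes are split by age at 80: below it they have one target, and "patients aged 80 and over without diabetes will have a target BP of <145/85 mm Hg". All patients with diabetes share a single target, whatever their age.

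Age appears once more in Statistical analysis, as a planned subgroup factor with a threshold of 65.

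**The concern.** A model that follows a minimised allocation should normally contain the factors that were balanced. Balancing a prognostic factor reduces the sampling variance of the treatment difference. If the factor is then omitted, the variation it explains stays in the residual, and the model's standard error does not register the gain. The interval comes out too wide and the p-value too large.

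Set against the minimisation list, the model covers three factors of four. Age is the exception. It is absent within the diabetic group and, among patients without diabetes, is reduced to one cut at 80, although the trial admits anyone aged 18 or over.

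What is at stake is a little precision in the reported interval and test. The omission may also carry over to the secondary BP analyses, which are to use similar techniques, and to the within-trial economic analysis, which takes its adjustments from the Statistical analysis section.

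**Working it through.** **1. Match factors to covariates.** Target level is read as a three-level factor.

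| Minimisation factor | In the primary model? |
|---|---|
| Baseline SBP | Yes, through baseline BP |
| Practice | Yes, as a random effect |
| Diabetes status | Yes, through target level (its own level) |
| Age | Only as under 80 versus 80 and over, in patients without diabetes |

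**2. Reproduce the plan's own figure.** Inputs from Sample size consideration: difference 5 mm Hg, SD 17 mm Hg, power 90%. Two-sided alpha of 0.05 is assumed, as none is stated.

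n per group = 2 × 17² × (1.960 + 1.282)² / 5² ≈ 243, against 244 stated. Power at 244 per group is 0.901. Dropout: 244 / 0.85 = 287.06, stated as 287, and 2 × 287 = 574. The sample size reproduces. (One-sided 0.05 would give 198, which does not.)

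**3. Standard error implied by the planning inputs.** The article states none. 17 × √(2/244) = 1.539 mm Hg. This is taken as the standard error that a model without age would report.

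**4. Effect of omitting age.** Let r be the partial correlation of age with 12-month SBP given the covariates already in the model. The article gives no value, so r is assumed. With near-perfect balance on age:

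- true SE = 1.539 × √(1 − r²)
- excess of the reported SE = 1/√(1 − r²) − 1
- actual type I error = 2 × [1 − Φ(1.96/√(1 − r²))]
- power without age = Φ[(5 − 1.96 × 1.539) / true SE]
- power with age = Φ[5 / true SE − 1.96]
- equivalent patients = 488 × [1/(1 − r²) − 1], where 488 = 2 × 244

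| Assumed r | True SE | Excess of reported SE | Type I error | Power without age | Power with age | Equivalent patients of 488 |
|---|---|---|---|---|---|---|
| 0.1 | 1.531 | 0.5% | 0.049 | 0.902 | 0.904 | 5 |
| 0.2 | 1.508 | 2.1% | 0.046 | 0.906 | 0.912 | 20 |
| 0.3 | 1.468 | 4.8% | 0.040 | 0.912 | 0.926 | 48 |

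For r = 0.3: 1.539 × √0.91 = 1.468; without age, (5 − 3.017)/1.468 = 1.351, so power is 0.912; with age, 5/1.468 − 1.96 = 1.446, so power is 0.926.

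The percentage excess does not depend on the SD. The figures are upper bounds, because balance will be less than perfect.

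**5. Check by simulation.** 488 patients, 80% minimisation with age split in two, target level in the model, practice effect omitted, 1,500 replicates. The age distribution (mean 66, SD 10) and 15% diabetes were assumed.

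| r | Model | Mean model SE | Empirical SE | Type I error |
|---|---|---|---|---|
| 0.1 | without age | 1.539 | 1.502 | 0.040 |
| 0.1 | with age | 1.534 | 1.498 | 0.040 |
| 0.2 | without age | 1.535 | 1.526 | 0.049 |
| 0.2 | with age | 1.512 | 1.512 | 0.049 |
| 0.3 | without age | 1.522 | 1.450 | 0.043 |
| 0.3 | with age | 1.470 | 1.436 | 0.047 |

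The Monte Carlo error of each type I figure is about √(0.05 × 0.95/1500) = 0.006, so these figures do not separate the models. The mean model SE does: at r = 0.3 it falls from 1.522 to 1.470 when age is added, and at r = 0.1 it hardly moves. The direction agrees with step 4.

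**The case against.** The best defence is that little is lost and the error is on the safe side. Three of the four factors are modelled, and target level carries part of the fourth. The r that counts is what remains after baseline BP, practice, target level and gender, and it may be small; at 0.1 the effect is negligible. Minimisation at 80% over four factors, one of them practice with around 95 practices expected, will not balance age perfectly, and the article does not say how age is grouped. All of this stands. It limits the size of the point but does not remove the mismatch.

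It could also be said that covariates belong to an analysis plan that is not shown. That does not answer the point, because the article fixes the list twice.

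Several stronger readings are tempting but unsupported:

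- A reader might infer that a stated standard error is wrong. The article states none; it gives an SD, and its sample size reproduces.
- A reader might infer that the analysis ignores the randomisation. It departs from it only for age below 80 and for age within the diabetic group.
- A reader might infer that nearly all patients fall below the cut at 80. The article gives no age distribution.
- A reader might count adjustment for gender as a fault because gender was not minimised on. Adjusting for a prespecified baseline covariate is legitimate.
- A reader might take the equivalent patients as a loss in the estimate itself. Under near-perfect balance the point estimate varies about equally with or without age; the cost falls on the reported interval and test.

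**Conclusion.** The point holds as a modest one. The mismatch is certain from the text: age is a minimisation factor and reaches the primary model only as a cut at 80 in patients without diabetes. The direction is also clear: if age is prognostic, the model-based standard error will be somewhat too wide and the test slightly conservative.

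The size is not known from the article. It rests on an assumed partial correlation and near-perfect balance. Across r = 0.1 to 0.3 the loss of power is 0.2, 0.7 and 1.4 percentage points (from the unrounded values: 0.9041 − 0.9024, 0.9124 − 0.9058, 0.9258 − 0.9116), and power stays above the planned 90% either way. There is no bias and no inflation of the type I error. The change is worth making because it is nearly free, not because the planned analysis would mislead.

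**What to change.** Add baseline age as a fixed-effect covariate to the primary SBP model, in both Outcomes and Statistical analysis, and to the secondary BP models that use similar techniques. Keep baseline BP, practice as a random effect, BP target level and gender as they are. The within-trial economic analysis refers back to the same adjustments and needs no separate edit.

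The cost is a few words in two sections and, with age as a single linear term, one degree of freedom. No new data are needed: age is already required for the minimisation, the BP targets and the subgroup at 65. The required sample size does not rise. The change should be recorded before any analysis by arm, so that it cannot be taken for a post hoc choice of covariate.

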#### Eligibility criteria

Eligibility criteria will aim to capture adult patients with treated but uncontrolled hypertension managed in primary care who will be aged 18 or over, have a Read code for hypertension in the clinical record (confirming hypertension), a current prescription of antihypertensive medication and a mean BP reading (calculated from the second and third BP readings) of >140/90 mm Hg taken during a baseline clinic appointment. Eligible patients will also be required to have access to the internet and be able to comprehend the website.

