#### Exclusion criteria

Exclusion criteria will include an inability to self-monitor (eg, diagnosis of dementia), a mean baseline BP reading of >180/110 mm Hg (stage 3 hypertension requiring more urgent intervention than would be available in the trial), hypertension not managed by family doctor (the trial facilitates primary care titration of medication), prescribed more than three antihypertensive medications (ie, resistant hypertension), chronic kidney disease (CKD) stage 4–5 or CKD stage 3 not managed by the GP (likely to be under specialist care and requiring different BP targets), terminal disease or other condition which in the opinion of the family doctor makes them inappropriate to take part, pregnant or breast feeding, a history of proteinuria (albumin creatinine Ratio (ACR) >30 mg/mmol) (different BP targets), postural hypotension (>20 mm Hg systolic drop after 1 min standing) (for whom intensification of BP medication may be inappropriate), atrial fibrillation (self-monitoring with oscillometric equipment not suitable), an acute cardiovascular event in the previous 3 months (BP and antihypertensive medication may not be stable) or a household member already enrolled on the study (to avoid bias). Participants who are involved in any other BP research will not be able to take part in the study.

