#### Participant flow through the study

At baseline, all patients will receive a consultation where informed consent will be taken, as well as clinical measures (confirmation of raised BP, height, weight) and medical history. Hypoglycaemic episodes in the last 6 months will be recorded for diabetic patients. BP will be measured after 5 min rest with a validated electronic automated sphygmomanometer (BP TRU BPM 200). Participants will be seated, and BP will be measured in their left arm unless there is a reason not to (principally lymphoedema or other medical condition). Six BP readings will be taken at intervals of 1 min, with the mean of the second and third readings used for the primary outcome. Patients will complete demographic measures and baseline assessments at home via HOME BP online, following which automatic allocation to intervention or usual care group will be triggered. Patients will be immediately notified of their allocation through HOME BP online, confirmed by email or letter. Practice staff will also be notified of patient group allocation by email. Participants will be informed that the research team will have access to their personal and study data to stay in touch with them throughout the study.

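### Minor improvement: test effect modification by baseline SBP and age on the continuous values, and keep the median and age-65 cuts for display

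*Protocol article*

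**What the plan says.** The Statistical analysis section of the protocol article plans subgroup analyses by BP target group and then by "older versus younger (65 as threshold), men versus women and better controlled at baseline versus worse controlled at baseline (median SBP". Sex and BP target group are categorical. Age and baseline SBP are not, and the section mentions no analysis of effect modification that uses them as continuous variables.

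Both values are in hand at baseline. The Randomisation section states: "Minimisation will be used taking into account participants' baseline SBP, age, diabetes status and practice". For BP, Participant flow through the study states: "Six BP readings will be taken at intervals of 1 min, with the mean of the second and third readings used for the primary outcome"; the same two readings decide eligibility. The primary model is described as "adjusting for baseline BP, practice (as a random effect), BP target levels and gender", so baseline BP is already a covariate. Age is not listed as one.

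The Economic analysis plan section carries the adjusted SBP outcome, with its subgroups, into the within-trial cost per unit reduction in SBP.

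**The concern.** Cutting a continuous modifier in two treats patients 1 mm Hg either side of the cut as different, and treats everyone on one side of it as alike. If the treatment effect changes gradually with starting BP or with age, the two-group contrast estimates that change less precisely than a slope would. The trial is sized for a main effect, so it has little precision for interactions to begin with.

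The SBP cut has a second weakness: it is the median of whoever enrols. Every participant is uncontrolled by the entry criterion, so the better-controlled group is simply the lower half of this sample. A reader cannot place a patient of their own on one side or the other without knowing where the median fell, and it would fall elsewhere in another population.

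What is at stake is how well the trial can say whether the effect depends on starting BP or age. The main comparison is not at stake.

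**Working it through.** **Inputs from the protocol article.** Sample size consideration: "90% power to detect a difference in SBP of 5 mm Hg (SD 17 mm Hg", 244 per group, 15% dropout, 287 per group and 574 in total. Entry limits for BP: "mean BP reading (calculated from the second and third BP readings) of >140/90 mm Hg" (Eligibility criteria), with exclusion for "a mean baseline BP reading of >180/110 mm Hg" (Exclusion criteria). Age: "who will be aged 18 or over". No mean, SD or shape is given for age or baseline SBP, and alpha is not stated; two-sided 0.05 is assumed.

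**1. The plan's own figure.** n per group = 2 x (1.960 + 1.282)^2 x 17^2 / 5^2 = 243. The t-test version gives 243.9, so 244. Then 244 / 0.85 = 287.06, rounded to 287, and 2 x 287 = 574. The stated figures reproduce. Analysed: 2 x 244 = 488.

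**2. Information kept after a cut.** For a linear arm-by-X interaction, the share of information kept by replacing X with the indicator X > c is corr(X, 1[X > c])^2. For normal X with a share p above c, where z is the standardised cut and phi the standard normal density, this equals phi(z)^2 / [p(1 - p)]. At the median it is 2/pi = 0.637, a loss of 36%.

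**3. Baseline SBP, cut at the median.** The distribution is assumed to be a normal truncated to 140-180 mm Hg.

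| Assumed distribution | Share kept | Loss |
|---|---|---|
| Parent mean 130, SD 10 (lowest of the cases run) | 0.570 | 43% |
| Parent mean 150, SD 12 | 0.670 | 33% |
| Parent mean 155, SD 20 (highest of the cases run) | 0.724 | 28% |
| Uniform limit | 0.750 | 25% |

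Over these truncated-normal cases (parent mean 130-155, SD 10-20) the sample median itself ranged from about 144 to 158 mm Hg, which shows how far the meaning of the cut depends on who enrols. Truncation at 140 is one reading of the entry limit. If raised diastolic BP alone qualifies, some SBP values lie below 140.

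**4. Age, cut at 65.** Assumed normal, mean 58-70, SD 8-12.
- Mean 58, SD 8: z = 0.875, p = 0.19, share kept 0.479, loss 52%.
- Mean 60, SD 10: z = 0.5, p = 0.31, share kept 0.581, loss 42%.
- Mean 65, any SD: z = 0, p = 0.50, share kept 0.637, loss 36%.

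The loss is smallest when 65 happens to be the median.

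**5. What this means for power (equal halves, N = 488, SD 17).**
- Split: SE of the difference between the two subgroup effects = 4 x 17 / sqrt(488) = 3.08 mm Hg. For a true difference of 5 mm Hg, 5 / 3.08 = 1.624, and power = Phi(1.624 - 1.960) = 0.37.
- Continuous term, normal modifier: the two half-means lie 2 x sqrt(2/pi) = 1.596 SD apart, so the same truth is a slope of 5 / 1.596 = 3.13 mm Hg per SD of the modifier. The SE of the slope is 2 x 17 / sqrt(488) = 1.54. The ratio is 2.036, and power = Phi(2.036 - 1.960) = 0.53.
- If the share kept is 0.75 instead, power with the continuous term is 47%; if 0.60, 55%.
- In sample-size terms, the split makes 488 patients count as 488 x 0.637 = 311.

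**6. Smallest difference detectable with 80% power.** Split: (1.960 + 0.842) x 3.08 = 8.6 mm Hg. Continuous term, on the same between-halves scale: 8.6 x sqrt(0.637) = 6.9 mm Hg. Both exceed the 5 mm Hg main effect.

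**The case against.** The strongest reply is that the article gives the subgroups one sentence, names the groups and does not say how effect modification will be tested. An analysis plan that is not shown may add continuous terms, and the named groups are compatible with that. The cuts are also fixed in advance, which guards against choosing them after seeing the results, and discrete groups have a use in the economic analysis. All of this is fair. It is why the point is an improvement to a secondary analysis, with no error or contradiction alleged, and why the fix keeps the groups. It does not remove the point: the article does fix the cuts, and the better method costs almost nothing.

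Three stronger readings are tempting and are not supported.
- A reader might infer that about a third of the information is lost as a matter of fact. The loss depends on roughly linear modification and on distributions that the document does not give. If the effect truly stepped at the cut, the split would lose nothing.
- A reader might extend the complaint about a sample-dependent cut to age. Age 65 is a fixed threshold and carries over to any population; only its information loss is at issue.
- A reader might take the 8.6 mm Hg detectable difference as harm done by the split. Most of it reflects the size of the trial. Any equal-halves contrast here has that limit, including sex if the sexes are balanced, and the continuous term only brings it down to about 6.9 mm Hg.

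**Conclusion.** The point holds as a minor, inexpensive improvement. Under roughly linear effect modification, the median SBP split gives up about 25-43% of the interaction information and the age-65 cut about 36-52%, over the assumed distributions shown. For equal halves, a normal modifier, 488 analysed and SD 17, power for a 5 mm Hg difference in effect is about 37% with the split and about 53% with the continuous term. The test therefore remains underpowered, and a null interaction should not be read as evidence of a constant effect under either method. The SD of 17 is used as stated; a smaller residual SD after adjustment would raise both powers and leave the share of information lost unchanged. The sample-median SBP cut has the further drawback that it means nothing fixed outside this trial. The primary analysis and the sex and BP-target subgroups are not affected.

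**What to change.** In the analysis plan, or in a sentence added to the subgroup paragraph:
- Base the effect-modification tests for baseline SBP and age on arm-by-continuous-value terms in the primary model, linear with one degree of freedom each. Enter baseline SBP as a continuous covariate and add the main effect of age, which the listed covariates do not include.
- Report the estimated treatment effect with its 95% CI at fixed values, for example 145, 155 and 165 mm Hg, and 55, 65 and 75 years.
- Keep the prespecified two-group estimates (median SBP, age 65) for display and for the economic subgroups, and give the observed median in mm Hg.
- State that conclusions about modification by these two variables rest on the continuous terms.

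The cost is wording and a few lines of analysis code; no new data are needed. The downside is that the terms assume approximate linearity, which one spline plot of treatment effect against each modifier can check.
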